### Secondary outcomes

3.6

(1)The DQOLS: the DQOLS 4-point scale contains 30 questions, involving psychological activities, such as embarrassment, despair, stress, pain (“very” to “no”) and social activities, such as daily life, social life, sexual life (“very bad” to “normal” or “very few” to “often”) and scoring 1 to 4 points from right to left. The cumulative score ranges from 30 to 100.(2)Score of pruritus degree: patient global assessment (PGA) “How serious is your skin pruritic now?” The patient's answer ranges from “no pruritic” to “intensively pruritic” and can be given with a score of 0 to 6.(3)Safety Assessment: the routine chemical examinations will be performed in 72 patients, at week 1 and 8 and will involve blood, urine analysis and fecal routine analyses, electrocardiogram, kidney and liver function assessments (ALT, AST, BUN, Cr, TBIL, GLU).

### Adverse events

3.7

(1)Ask and record the adverse events and degree of patients at each consultation after medication, and record, in details, the symptoms, occurrence, duration and disappearance times of adverse events.(2)The correlation between adverse events and drugs is assessed according to whether they are unrelated, possibly unrelated, possibly relevant, or relevant.(3)Incidence of adverse events = number of adverse events / total cases × 100%.(4)After treatment, the patients’ tolerance to drugs will be evaluated according to poor, moderate, light and high praise.

If adverse events occur or there were abnormal blood test results of liver and kidney function, the subjects will be advised to discontinue all drug treatments related to the test and seek medical advice from doctors for a safe continuation of the study.

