**Methods and analysis::**

This is a pilot randomized controlled trial with the objective of investigating the effect of Jia Wei Liang Xue Xiao Feng San granules on relapse rate of recurrent PV and the correlation between Psoriasis area severity index (PASI) and key psoriasis-related cytokine changes and the number of cells. A total of 102 participants were recruited for this study, including 72 patients with recurrent PV, 15 healthy volunteers and 15 patients with psoriasis vulgaris who have recovered for more than 1 year. A total of 72 patients, with recurrent PV, will be randomized (1:1) to receive the oral Chinese herbal medicine Jia Wei Liang Xue Xiao Feng San or the oral Acitretin Capsule treatments for a period of 8 weeks. After this period, participants whose PASI scores improvement reached more than 75%, will undergo a 52-week follow-up phase.

The primary outcome measures are as follows:

The secondary study outcomes will include:

This trial may provide a novel regimen for recurrent PV patients if the granules decrease recurrence rate without further adverse effects.

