**Figure 1 F1:**
[figure not shown]
Test flow chart.

Potential participants will be invited to an initial assessment (first visit) consisting of an inclusion and exclusion criteria screening. If eligible, participants will be asked for informed consent and will undergo assessment of Psoriasis area severity index (PASI), dermatology life quality index (DQOLS), and score of Pruritus Degree by PGA, lesion photos and vital signs, full blood count, kidney and liver function blood tests, electrocardiogram, stool examination and urine (routine chemical examinations).

A total of 72 patients with recurrent PV will be randomized (in a 1:1 ratio) to receive oral Chinese herbal medicine JWLXXF or oral acitretin for 8 weeks. During the observation phase, psoriasis symptom measures will be self-reported by participants and recorded in a daily or weekly diary. Face-to-face assessments with blinded assessors will be scheduled at weeks 2, 4, 6, and 8 (Fifth visit), with further data collected, including assessment of PASI, DQOLS, and score of Pruritus degree by PGA, lesion photos, drug adherence, vital signs, adverse events and cause analysis of shedding (Table 1). The conversation will be made to 72 patients, at the time of medical treatment, to check adherence to the dosage guidelines and to monitor adverse events. Routine chemical examinations, laboratory assessments of efficacy and safety evaluation will also be scheduled at the end of the 8-week period.

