#### Primary outcomes

3.5.1

(1)PASI: assess the severity of the disease.(2)Laboratory assessments: the number and distribution of Th1, Th2, Th17, Treg, Th22, and Th9 cells will be determined by ELISA. The expression of the transcription factors T-bet, GATA3, ROR gamma t, Foxp3 gene will be investigated by PCR and WB. The screening of cytokines, such as IFN-gamma, IL-4, IL-17A, IL-17F, IL-22, TGF-beta, IL-10 and IL-9 will be performed by Bio-Plex suspension chip.(3)Recurrence rate = recurrence cases/follow-up cases ∗100%

Note:

No recurrence criteria: the same as the end of treatment and lesion limitation. Recurrence criteria: new skin lesions appearing in the patients who were clinically cured or have the original skin lesions expanding, the color turning red, the scale increasing and the PASI score increasing for ≥ 1.

(1) Mitigation period: this remission period - the last remission period.

Note:

The last remission period: the time from the last clinical cure to the recurrence. This remission: the time interval from the end of JWLXXF treatment to the next recurrence.

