### Sample size calculation

3.8

Due to the unknown potential primary outcome at this stage, the sample size was calculated by reference to a standardized effect size. An effect size of 0.9 SD was chosen with consideration of the drug cost and patients’ motivation to adhere to the treatment. To detect a difference of 0.9 SD with 90% power using a 5% significance level, a sample size of 30 per arm would be required. Considering 20% dropout rate, the total sample size should be adjusted to 36 for each group.

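### The adverse-event incidence formula divides events by patients, so it is not the proportion of patients affected, can exceed 100% and could misrank the arms

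*Protocol article*

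**What the plan says.** Section 3.7 (Adverse events) of the protocol article defines "Incidence of adverse events = number of adverse events / total cases" and expresses the result as a percentage. The first item of the same section tells staff to "Ask and record the adverse events and degree of patients at each consultation after medication" and to note each event's symptoms, onset, duration and end. Section 2 (Methods/design) schedules four face-to-face assessments on treatment, at weeks 2, 4, 6 and 8. Nothing in the article limits the numerator to one event per patient or to patients with an event.

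The other percentage that the article defines is built differently. Section 3.5.1 (Primary outcomes) has "Recurrence rate = recurrence cases/follow-up cases", which is patients over patients.

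The abstract ties the trial's promise partly to safety: the granules may offer a new regimen "if the granules decrease recurrence rate without further adverse effects".

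**The concern.** An incidence given as a percentage is read as the share of patients who had the event. The stated formula yields that share only if every affected patient has exactly one event. Otherwise it is the mean number of events per patient, multiplied by 100 and labelled as an incidence.

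Two things follow. The figure has no ceiling at 100%. A comparison between the arms also mixes how many patients were affected with how many events each of them had. A few patients with several events could make one drug look worse although fewer of its patients were affected. This is the only summary measure for adverse events that the article defines, and the article looks to safety as part of the case for the granules.

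**Working it through.** **Inputs**
- Formula: section 3.7, as quoted above.
- Patients per arm: section 3.8 (Sample size calculation), "the total sample size should be adjusted to 36 for each group", so N = 36.
- Adverse-event counts: none are given. All counts below are assumptions chosen to show how the formula behaves; they are not forecasts. There is no stated figure to reproduce.

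**Relation between the two measures**

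Let k be the patients with at least one event, E the number of events, and m = E/k the mean number of events per affected patient.
- Protocol formula: E/N × 100% = m × (k/N × 100%).
- Proportion of patients affected: k/N × 100%.

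The formula therefore overstates the proportion by the factor m. The two agree only at m = 1.

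**When the formula exceeds 100%**

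This needs E > 36, that is k > 36/m.

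| Mean events per affected patient (m) | Patients affected must exceed (of 36) |
|---|---|
| 1 | 36 (impossible) |
| 1.5 | 24 |
| 2 | 18 |
| 3 | 12 |
| 4 | 9 |

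For example, 10 patients with 4 events each give 40/36 = 111.1% by the formula, against 10/36 = 27.8% of patients.

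**When the arms change order**

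| Assumed counts, 36 per arm | Patients affected | Events | Protocol formula | Proportion of patients |
|---|---|---|---|---|
| Arm A | 6 | 24 | 24/36 = 66.7% | 6/36 = 16.7% |
| Arm B | 12 | 14 | 14/36 = 38.9% | 12/36 = 33.3% |

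By the formula A looks worse; by patients B has twice as many affected. The order reverses when the ratio of events per affected patient (A to B) exceeds the ratio of affected patients (B to A). Here the first ratio is (24/6)/(14/12) = 4/1.17 = 3.4 and the second is 12/6 = 2. With the same m in both arms the order is kept, although each figure is still inflated by m.

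**The case against.** The best defence is that the authors meant patients with an adverse event. They call the result an incidence, multiply it by 100%, and build the recurrence rate as cases over cases; the English is loose in places. That reading is plausible, and on it the point is one of wording. No text restricts the numerator, however, so an analyst who follows the formula would count events.

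A second defence is that repeat events may be few, because after an adverse event "the subjects will be advised to discontinue all drug treatments related to the test". That may reduce repeats. It does not prevent several events at one visit, and it is not part of the definition.

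A reader might also infer stronger points, which the document does not support:
- **That a chi-square test on this figure would be invalid.** Section 3.10 (Statistical analysis) assigns that test to baseline characteristics and primary outcomes. It names no test for adverse events.
- **That a persistent complaint is counted again at each visit.** Onset, duration and end are recorded, so it can be counted once. Only distinct or recurrent events inflate the numerator.
- **That a figure above 100% or a reversed ranking is to be expected.** Both are possible, but without event rates neither can be called likely.
- **That the safety judgement rests on this ratio alone.** Degree and relation to the drug are also assessed (section 3.7), and laboratory and ECG assessments are listed as a secondary outcome (section 3.6).

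Finally, an events-per-patient ratio is a legitimate measure if it is labelled as such. The fault is in calling it an incidence percentage.

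**Conclusion.** The point holds as a wrongly stated definition. It is not a detail left to a fuller document, because the article gives the formula outright. Taken as written, the formula overstates the proportion of patients affected by a factor equal to the mean number of events per affected patient: no error at 1, a doubling at 2. It exceeds 100% once an arm of 36 has more than 36 events, and it can reverse the order of the arms if events per affected patient differ enough between them.

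This rests on the literal reading of the formula and on 36 patients per arm. How far it would distort this trial's results cannot be known from the document. It should be corrected, but it does not undermine the design.

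**What to change.** Replace the formula in section 3.7 with the following, computed for each arm: incidence of adverse events = patients with at least one adverse event / patients who took at least one dose × 100%. Report the number of events separately, as a count or as events per patient, under that name.

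Naming the denominator also settles what total cases means. That is useful because the elimination criteria (section 3.1.3) list allergy to the study drugs and stopping treatment, so a reader could wonder whether such patients still count.

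The cost is a one-line change. Section 3.7 already has events asked about and recorded for patients at each consultation, so no new data should be needed even though recruitment has begun. If the authors meant patients with an event all along, the change only makes the text say so.

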## Methods/design

2

This is a pilot randomized controlled trial for 3 years. In this study, a total of 102 participants will be enrolled, including 72 patients with recurrent PV, 15 healthy volunteers and 15 patients with psoriasis vulgaris who have recovered for more than 1 year. The entire trial consists of an initial assessment, a one-week screening phase (week 1), an 8-week observation phase (week 1 to week 8) and a 52-week follow-up phase (week 9 to week 60) (Fig. 1).

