#### Exclusion criteria

3.1.2

People with any of the following will be excluded from participation:

(1)psoriasis with other skin diseases;(2)those with a known cancer, infection, electrolyte imbalance, acid-base disturbance or calcium metabolic disorder, known disorders of calcium metabolism (high blood calcium levels);(3)psychotic patients (self-assessment anxiety scale (SAS) scores > 50 or self-assessment depression scale scores > 53, or other psychiatric scores), hyperlipidemia, high vitamin A, pregnant and lactating, or plan to become pregnant within a year;(4)types of psoriatic arthritis or pustular psoriasis or erythroderma psoriaticum;(5)taking systemic drugs or phototherapy for psoriasis within the 4 weeks prior to screening and taking topical drug treatment for psoriasis within the 2 weeks prior to screening.

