#### Inclusion criteria of healthy volunteers

3.1.4

Healthy volunteers’ inclusion criteria:

(1)aged between 18 and 65 years;(2)no family history of psoriasis;(3)people who did not use corticosteroids or immune agents within a month of the trial;(4)people without serious systemic diseases, tumors, immunodeficiency, or mental disorders.

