### Randomization

3.4

Unpredictable randomized sequences were generated by computer and sealed in opaque and sequentially encoded envelopes. After determining the eligibility of the participants, the researchers will break the envelopes in order and assigned them to the appropriate test group. The person who will generate the random sequence will not be the same person as the assigned subject, and the random assignment will not be displayed until the end of the study.

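### The 72 treated patients have no liver or kidney entry criterion, and the first-visit liver and kidney results are not used before randomisation

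*Protocol article*

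**What the plan says.** **Eligibility.** Section 3.1.1 admits patients on diagnosis, syndrome, age (18 to 70), consent and type of recurrence. Section 3.1.2 excludes, among other things, "electrolyte imbalance, acid-base disturbance or calcium metabolic disorder, known disorders of calcium metabolism (high blood calcium levels" and "hyperlipidemia, high vitamin A, pregnant and lactating, or plan to become pregnant within a year", and gives numerical cut-offs for anxiety and depression scores. Section 3.1.3 adds drug allergy, non-adherence, incomplete records and major events during the trial. None of the three lists has a liver or kidney item.

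**Tests at entry.** Section 2 says that patients found eligible are asked for consent and then assessed. The assessment includes "full blood count, kidney and liver function blood tests, electrocardiogram, stool examination and urine (routine chemical examinations". Section 3.6 schedules the routine laboratory tests at weeks 1 and 8 and names the analytes: ALT, AST, BUN, Cr, TBIL and GLU.

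**Randomisation.** Section 3.4: "After determining the eligibility of the participants, the researchers will break the envelopes in order".

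**Action on abnormal results.** Section 3.7 says that, if there are "abnormal blood test results of liver and kidney function, the subjects will be advised to discontinue all drug treatments related to the test", and that they should "seek medical advice from doctors for a safe continuation of the study".

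**The concern.** The plan regards an abnormal liver or kidney result as serious enough to advise a patient to stop the trial drug. It does not regard the same result as a reason not to start. The information needed is already collected at the first visit, yet nothing in the printed text makes anyone act on it before allocation.

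What is at stake is patient safety. A patient aged up to 70 with existing liver or kidney impairment could take the herbal granules or acitretin for 8 weeks while the result showing the impairment is on file. There is a smaller cost to interpretation. Liver and kidney tests are part of the safety outcome in section 3.6, and patients who enter with abnormal values make the week 8 results harder to read.

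**Working it through.** The article gives no figure on this point to reproduce. The check is a comparison of sections, followed by a count of whom an amendment could still reach.

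**1. Do the lists use the results?** Section 3.6 names 6 analytes. GLU is glucose, which leaves 6 − 1 = 5 liver or kidney markers (ALT, AST, TBIL, BUN, Cr). The number of these that appear in sections 3.1.1 to 3.1.3 is 0. No diagnosis of liver or kidney disease appears there either.

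**2. Does the order of events catch the patient another way?** The printed sequence is: check the inclusion and exclusion criteria; if eligible, obtain consent; take the bloods; open the next envelope once eligibility is determined. Because no criterion refers to the bloods, eligibility can be settled without them. A team following the text exactly would randomise a patient with a clearly abnormal entry value.

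**3. Is there time to read the results?** Yes. Section 2 sets out "a one-week screening phase (week 1), an 8-week observation phase (week 1 to week 8", so a screening week exists in which results could be returned and acted on. The two phases share the label week 1, so the text does not itself fix that the results are read first.

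**4. Would later monitoring catch the patient?** Only in part. After week 1 the next scheduled laboratory test is at week 8, and section 2 places it at the end of treatment. Between the two, only an unscheduled test would bring the advice in section 3.7 into play.

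**5. How many patients are affected?** This cannot be derived. The documents give no frequency of abnormal liver or kidney results in this population.

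**6. Whom could a change still reach?** Inputs: 72 treated patients and 15 recovered psoriasis patients planned (section 2), and 60 patients recruited so far (section 4.4). The article does not say how the 60 divide.
- If all 60 have recurrent psoriasis: 72 − 60 = 12 still to enter, 60 already enrolled.
- If the 60 include all 15 recovered patients (assumption): 60 − 15 = 45 already enrolled, 72 − 45 = 27 still to enter.

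The criterion would therefore apply to 12 to 27 new entrants, and a file review to 45 to 60 patients already enrolled.

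**The case against.** The strongest reply is that this is a journal article. The full protocol is not shown, and the schedule of evaluations and the flow chart are missing from the text at hand, so a laboratory limit may exist elsewhere. That explains a missing numerical limit better than a missing criterion. The article prints numbered eligibility lists that go down to psychiatric score cut-offs and name metabolic exclusions, and a protocol article does not commonly leave out whole eligibility items. If the full protocol does hold a criterion, the remedy shrinks to stating it in the list.

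A second reply is that the documents state no liver or kidney hazard for either drug, and section 4.1 even credits two of the herbs with protecting the liver. This is fair and limits the weight of the point. It does not remove the inconsistency, because section 3.7 itself singles out these two organs as grounds for advising a stop.

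Third, it is tempting to contrast the patients with the healthy volunteers, who must be "people without serious systemic diseases, tumors, immunodeficiency, or mental disorders". That requirement fits a clean immunological reference group, so it is not evidence that a drug-safety criterion was withheld from the patients. The point does not rest on it.

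Finally, a reader might infer that section 3.7 is itself defective: that with no threshold and no baseline comparison it would take patients off treatment for trivial or long-standing abnormalities. The documents do not support that. The provision is advice, coupled with the instruction to "seek medical advice from doctors for a safe continuation of the study", so a doctor stands between the result and any stop. The entry value is collected and available for comparison. With scheduled tests only at weeks 1 and 8, little treatment is left to stop at the second test. Nor does the article say that any out-of-range value counts as abnormal, so no stopping rate can be worked out from it.

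**Conclusion.** The concern stands for entry. On the printed text, a patient with a clinically relevant abnormal entry ALT, AST, TBIL, BUN or Cr can be randomised and dosed, although the results are collected beforehand and section 3.7 treats abnormal results of this kind as a reason to advise stopping. This is a worthwhile, inexpensive safety correction, held with medium confidence because the full protocol is not shown.

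Its size in patients is unknown. The figures of 12 to 27 describe only the reach of an amendment, and the upper one assumes that the 60 recruited include all 15 recovered patients. The point does not extend to the primary outcomes or their analysis. Nor does it extend to the stopping advice, where the absence of a stated limit is a matter of wording.

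**What to change.** - Add to section 3.1.2 an exclusion for clinically significant liver or kidney abnormality at entry, covering ALT, AST, TBIL, BUN and Cr, with a limit per analyte set by the investigators. It should not exclude every trivial out-of-range value.
- State in sections 2 and 3.4 that the results are read within the one-week screening phase, before the envelope is opened.
- Review the entry results on file for the 45 to 60 recurrent psoriasis patients already enrolled, and seek medical advice for any beyond the limit.
- If the full protocol already holds such a criterion, state it in the eligibility list.
- As a wording note only, section 3.7 could say that results are read against the patient's entry value.

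**Cost:** a few more screen failures, a short amendment that reaches only the remaining 12 to 27 entrants, and the file review. No additional blood sample is needed. If recruitment has finished since the status in section 4.4, only the file review still has effect.

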### Sample size calculation

3.8

Due to the unknown potential primary outcome at this stage, the sample size was calculated by reference to a standardized effect size. An effect size of 0.9 SD was chosen with consideration of the drug cost and patients’ motivation to adhere to the treatment. To detect a difference of 0.9 SD with 90% power using a 5% significance level, a sample size of 30 per arm would be required. Considering 20% dropout rate, the total sample size should be adjusted to 36 for each group.

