**Table 1 T1:**
[figure not shown]
Evaluation measures and time points.

The 72 patients with recurrent PV, whose PASI scores improvement are more than 75%, will undergo a 52-week follow-up phase (week 9 to week 60), with further data collection, including assessment of PASI, routine chemical examinations, recurrence rate, remission period (This remission period - the last remission period) (Table 1).

For the 52-week follow-up phase, participants will continue to record symptoms in their daily or weekly diaries. At week 60, participants will attend an end of follow-up assessment (9th visit) which will mark the end of the trial.

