### Statistical analysis

3.10

SPSS Statistics 17.0 (IBM SPSS Inc., Armonk, NY) will be used for the statistical analysis of data, which will be carried out by independent statisticians. The Chi-square test will be used to evaluate the basic baseline characteristics and primary outcomes of the 2 groups. The Spearman rank correlation analysis of the correlation between PASI and biochemical indexes, will be used. The secondary outcomes will be evaluated by means, standard deviations and medians. The one way ANOVA test will be used to compare the mean of multiple samples, the LSD test for the homogeneous variance, and the Tamhane T2 test for the uneven variance. *P* < .05 will be considered as statistically significant.

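### The 90% power in section 3.8 is for an unnamed 0.9 SD difference in means and does not carry over to recurrence rate, a primary outcome counted only in PASI75 responders

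*Protocol article*

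**What the plan says.** Section 3.8 (Sample size calculation) gives the reason for a generic effect size: "Due to the unknown potential primary outcome at this stage, the sample size was calculated by reference to a standardized effect size". The size of that effect is explained only by practical considerations: "An effect size of 0.9 SD was chosen with consideration of the drug cost and patients’ motivation to adhere to the treatment". The calculation follows: "To detect a difference of 0.9 SD with 90% power using a 5% significance level, a sample size of 30 per arm". The inflation is: "Considering 20% dropout rate, the total sample size should be adjusted to 36 for each group".

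Section 3.5.1 does name primary outcomes: PASI, a set of laboratory measures, the recurrence rate (recurrences divided by patients followed up) and, listed after these, a remission-period difference. The Abstract gives the effect on relapse rate as part of the objective, beside the correlation of PASI with cytokines and cell counts.

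Section 2 (Methods/design) limits who enters follow-up: "The 72 patients with recurrent PV, whose PASI scores improvement are more than 75%, will undergo a 52-week follow-up phase". Section 4.2 repeats the PASI75 condition. Section 3.10 (Statistical analysis) fixes the test: "The Chi-square test will be used to evaluate the basic baseline characteristics and primary outcomes of the 2 groups".

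**The concern.** A 0.9 SD effect describes a difference between two means. Recurrence is a proportion. It is also observed only in the part of each arm that responds at week 8, and the 20% allowance in section 3.8 is for dropout, not for non-response. So both the effect scale and the number of patients behind the 90% figure differ from those of the recurrence comparison.

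Section 3.8 attaches its one power figure to no outcome, so a reader will attach it to the outcomes in section 3.5.1, recurrence included. A non-significant recurrence comparison could then be read as a negative result from a trial with 90% power.

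**Working it through.** **1. The plan's own figure.** Inputs from section 3.8: 0.9 SD, 90% power, 5% level (sidedness not stated; two-sided assumed), 20% dropout. Equal allocation is from section 2: "A total of 72 patients with recurrent PV will be randomized (in a 1:1 ratio) to receive oral Chinese herbal medicine JWLXXF or oral acitretin".

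- Normal approximation: n = 2 × (1.960 + 1.282)² / 0.9² = 25.9, so 26 per arm.
- Two-sample t-test (noncentral t): 26.94, so 27 per arm. The stated 30 is slightly larger and gives 92.9% power.
- Inflation: 30 × 1.2 = 36. Dividing by the retained share instead gives 30 / 0.8 = 37.5, so 38.
- What 36 leaves after 20% loss: 36 × 0.8 = 28.8 per arm, with 92% power for 0.9 SD.

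For a mean difference in an outcome measured in all randomised patients, the 90% is therefore met, even after dropout.

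**2. Patients available for recurrence.** The document gives no PASI75 rate for either arm. Its only response figure is 73.33% in an earlier 30-case series of the herbal compound (section 4.1), which is not stated to be PASI75. I use it as an optimistic value and add 50% and 30% as assumptions, the same in both arms:

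- 28.8 × 0.30 = 8.6, about 9 per arm
- 28.8 × 0.50 = 14.4, about 14 per arm
- 28.8 × 0.733 = 21.1, about 21 per arm

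**3. Power for recurrence.** The document states no recurrence rates. I assume 60% in one arm and 40%, 30% or 20% in the other. Power is the exact binomial probability that the Pearson chi-square statistic (no continuity correction) passes its 5% critical value. The 95% CI half-width for 60% v 30% is 1.96 × √[(0.6×0.4 + 0.3×0.7)/n] = 1.96 × √(0.45/n).

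| Responders per arm | 60% v 40% | 60% v 30% | 60% v 20% | CI half-width, 60% v 30% |
|---|---|---|---|---|
| 9 | 13% | 24% | 43% | ±44 points |
| 14 | 16% | 33% | 58% | ±35 points |
| 21 | 24% | 49% | 78% | ±29 points |

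Starting from 60%, 90% power would need recurrence to fall to about 14% with 21 per arm, or about 7% with 14 per arm. As an upper bound, if all 36 per arm responded and none were lost, power would be 73% for 60% v 30% and 95% for 60% v 20%.

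**4. Remission period.** This is a duration, so a standardised mean difference is at least on the right scale, but it is measured in the same follow-up group. For 0.9 SD, t-test power is about 81% at 21 per arm and 63% at 14.

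**The case against.** The trial is called a pilot, and section 3.8 says openly that it rests on a generic effect size. It nowhere claims 90% power for recurrence in so many words. PASI stands first among the primary outcomes, and 0.9 SD is a sensible scale for it. This stands in part: it limits the harm and shows that the calculation can be made to fit one listed outcome. It does not remove the mismatch. A pilot need not be powered, but this one states 90% power and tests its primary outcomes at P < .05, and the reason given for a generic effect conflicts with the list in section 3.5.1.

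Two stronger readings are tempting, and the document supports neither.

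- A reader might infer that the design has some fixed low power for recurrence, say 25–50%. That range comes from one assumed pair of recurrence rates and assumed response rates, none of which the plan states. Larger effects give more. If 0.9 is read as a difference on the arcsine scale (for example 70% v 27%), 20 to 22 per arm gives about 81–85% by normal approximation.
- A reader might infer that wrong arithmetic leaves the trial too small, because a t-test needs 27 rather than 30 and keeping 30 would need 38 rather than 36. Both differences are real under those formulas, but neither matters here. The 30 errs on the safe side, a rank-test allowance gives 29 (26.94 × π/3 = 28.2), and 36 covers the 34 obtained from 27 / 0.8 = 33.75.

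**Conclusion.** The point holds in limited form. The 90% in section 3.8 belongs to a difference in means in all randomised patients. It does not apply to recurrence rate, which is a proportion, tested by chi-square, in PASI75 responders only. Nor does it apply to the remission period, which is measured in those same responders. Nothing else in the document supplies a power figure for either, and the statement that the primary outcome is unknown contradicts section 3.5.1.

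The size of the shortfall for recurrence cannot be fixed from the document. For differences of 20 to 40 points from 60% and 9 to 21 responders per arm, power runs from 13% to 78%. That range rests on assumed recurrence rates, assumed response rates equal in both arms, and the plan's 20% dropout. The conclusion that the 90% does not transfer rests on none of these assumptions.

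**What to change.** Keep the 72 patients and revise the text.

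- In section 3.8, name the outcome to which the 0.9 SD applies. It should be one measured in all randomised patients. The choice is the sponsor's; week-8 PASI is one candidate.
- In section 3.10, give that outcome a test that compares means in place of the chi-square now assigned to all primary outcomes.
- Remove the statement that the primary outcome is unknown.
- State that recurrence is not powered at 90%. Give the expected responders per arm, with power and CI width as a range under stated response and recurrence rates, as in the table above.
- Optionally, note that 27 per arm suffices for 0.9 SD (two-sided 5%, t-test) and that 36 enrolled less 20% leaves about 29, with 92% power.

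The cost is wording and a less favourable stated figure for recurrence. No extra patients are needed, which matters because section 4.4 reports 60 patients already recruited.
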